### Statistical analyses

The study design involves a two group Randomised trial with five assessment points. As the hypotheses involve comparisons of the rate of change with which men in the treatment versus control groups will achieve optimal physical and psychological QoL, the appropriate analysis is a two level multilevel model (with Level 2 = men and Level 1 = Assessment points). These analyses will be adjusted to account for equivalence testing procedures where appropriate with respect to the hypotheses. Although power models are not articulated for multilevel analysis as clearly as they are for ordinary linear modelling, the Optimal Design software of Raudenbush [29] and the simulation work of Jo [30] suggest appropriate sample sizes. Assuming that at least 70% of the men in each group will remain in the study (this is highly conservative as we have previously demonstrated only a 10% attrition rate in QoL studies with men with PCa) and assuming further moderate effect size of d = 0.5 and alpha at .05, a total sample size if 400 (i.e. 200 per group) would result in over 90% power.

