## Methods/design

### Study aims and hypotheses

The study aims are to assess the quality of life effects of robotic surgery compared with open prostatectomy; determine the economic costs of robotic versus open prostatectomy with regards to both health sector costs and direct and indirect cost to patients; evaluate life expectancy profiles of patients receiving both forms of prostatectomy.

We hypothesise that:

1. There will be no difference between the two groups in terms of surgical and clinical indices of oncological outcome.

2. Patients randomised to robotic prostatectomy will have improved short term (3 months postoperative) quality of life outcomes compared with those randomised to open prostatectomy with regards to pain, physical functioning, fatigue; summary (AQoL-8D and SF36) and domain specific quality of life (urinary incontinence, bowel function and erectile function), time to return to usual activities.

3. Patients randomised to open prostatectomy will have comparable medium (6–12 months) and long term (24 months) quality of life outcomes compared with those randomised to robotic prostatectomy with regards to pain, physical functioning, fatigue; summary (AQoL-8D and SF36) and domain specific quality of life (urinary incontinence, bowel function and erectile function).

4. There will be no difference between the two groups with regards to psychological distress, cancer specific distress and decision-related distress.

5. There will be a short-term and overall cost advantage for open prostatectomy.

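### The analysis is justified as a rate-of-change comparison, but the hypotheses are set at named times, and the sign of a rate depends on how it is read

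*Protocol article*

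**What the plan says.** Under Study aims and hypotheses, the QoL hypotheses are tied to times after surgery.

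- Hypothesis 2: "Patients randomised to robotic prostatectomy will have improved short term (3 months postoperative) quality of life outcomes compared with those randomised to open prostatectomy".
- Hypothesis 3: men in the open arm "will have comparable medium (6–12 months) and long term (24 months) quality of life outcomes" relative to the robotic arm.
- Hypothesis 4 concerns distress and carries no rate: "There will be no difference between the two groups with regards to psychological distress, cancer specific distress and decision-related distress".

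Hypothesis 1 expects no oncological difference, and hypothesis 5 concerns cost. None of the five mentions a rate of change. The nearest is time to return to usual activities in hypothesis 2, which is a duration and not a rate of change in a score.

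The Statistical analyses section gives a different account. It opens its rationale with "As the hypotheses involve comparisons of the rate of change with which men in the treatment versus control groups will achieve optimal", completes the sentence with physical and psychological QoL, and concludes that "the appropriate analysis is a two level multilevel model (with Level 2 = men and Level 1 = Assessment points"). It then adds: "These analyses will be adjusted to account for equivalence testing procedures where appropriate with respect to the hypotheses". It does not say how time is coded, or whether a single slope is the test.

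**The concern.** The sentence that selects the analysis misdescribes what is to be tested. A statistical analysis plan may settle how time enters the model, but these two sections would still name different targets.

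The mismatch has consequences because of the pattern the trial expects. Hypotheses 2 and 3 together describe a gap in favour of robotic that is present at 3 months and has closed by 6–12 and 24 months. For the gap to close, open must improve faster than robotic after 3 months. A comparison of rates that spans the closing phase therefore credits open with the better rate, while one confined to the opening phase credits robotic. An analyst who follows the stated rationale could obtain either sign from the same data, and neither result would answer the 3-month or the 24-month question.

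**Working it through.** **1. The plan's own power figure.** Inputs from Statistical analyses: 200 per group, 70% retained, d = 0.5, alpha 0.05 (taken as two-sided).

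- Analysable per arm: 200 × 0.70 = 140.
- SE of a difference in means, in SD units: √(2/140) = 0.1195.
- 0.5 / 0.1195 = 4.18. Power = Φ(4.18 − 1.96) = Φ(2.22) = 98.7%.

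This agrees with the stated figure of over 90%. It is the power of a two-mean comparison at one time, which is the form of hypothesis 2.

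**2. One slope over the full follow-up.** Visits are those of the Abstract: 0, 1.5, 3, 6, 12 and 24 months. The article gives no effect trajectory and no within-man correlation, so these are assumed: arm differences (robotic minus open) of 0, 0.5, 0.5, 0, 0, 0 SD; equal correlation ρ between visits; baseline left unconstrained.

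- Mean time: 46.5 / 6 = 7.75 months.
- Sxx = 60.0625 + 39.0625 + 22.5625 + 3.0625 + 18.0625 + 264.0625 = 406.875.
- Sxy = 0.5 × (1.5 − 7.75) + 0.5 × (3 − 7.75) = −5.5.
- Slope difference = −5.5 / 406.875 = −0.0135 SD per month, or −0.324 SD over 24 months.
- SE = √[(2/140)(1 − ρ) / 406.875].

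| ρ | SE | z | Chance of a significant result against robotic |
|---|---|---|---|
| 0.3 | 0.00496 | −2.7 | 78% |
| 0.5 | 0.00419 | −3.2 | 90% |
| 0.7 | 0.00325 | −4.2 | 99% |

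Under these assumptions robotic is never worse at any visit.

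**3. Sensitivity to the reading.** The article gives the number of assessments differently in the Abstract (baseline plus five), the Background (baseline plus seven) and Statistical analyses (five points), so all were tried.

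- Five post-operative visits, months: −0.474 SD, z = −3.9 to −5.9.
- Eight visits, months: −0.335 SD, z = −3.1 to −4.8.
- Baseline plus five, log time, slower fade of the benefit (the weakest unconstrained case): −0.17 SD, z = −1.4 to −2.1.
- Baseline plus five, baseline constrained equal, ρ = 0.5: −0.01 to −0.24 SD, depending on time coding and effect pattern.

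A whole-follow-up slope is negative in every case tried, but its size ranges from clearly significant to nearly nothing.

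**4. A rate over the early phase only.** Visits 0, 1.5 and 3 months: Sxx = 4.5 and Sxy = 1.5 × 0.5 = 0.75. The slope difference is 0.75 / 4.5 = +0.167 SD per month, or +0.5 SD over 3 months, with z = 3.5, 4.2 and 5.4 for ρ = 0.3, 0.5 and 0.7. The sign is opposite to that in step 2.

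**The case against.** The strongest reply is that the article never states a single linear slope. The model it names can carry time-specific contrasts. The phrase about the rate at which men reach optimal QoL can fairly be read as speed of recovery, on which earlier recovery favours robotic. The equivalence sentence refers back to the hypotheses and so bears on hypotheses 3 and 4. Time coding, baseline handling and named contrasts are commonly left to a fuller plan that is not shown.

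Most of this stands. A reader might infer that the planned analysis would favour open surgery and reverse the QoL conclusion. The documents do not support that: it needs one slope over all visits to be the test, plus an assumed trajectory and correlation, and the article fixes none of these. A reader might also infer that the model would be forced onto margin status or time to return to usual activities. The article ties the model to QoL, and silence on other outcomes in a condensed article is not an error.

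What the reply does not remove is the conflict between the two sections. The equivalence sentence names no time point, and it leaves the rate-of-change rationale in place.

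**Conclusion.** The point holds as an internal contradiction with a conditional consequence. The stated target, a rate of change, is not what hypotheses 2 and 3 assert, and comparing rates tests neither. If the rate is one slope over full follow-up with baseline unconstrained, the expected pattern gives z of about −2.7 to −4.2 against robotic on the Abstract's schedule in months. With baseline constrained equal the slope can be close to zero, and over baseline to 3 months it favours robotic. These figures rest on assumed differences of 0.5 SD at 6 weeks and 3 months and none elsewhere, 140 men per arm, and within-man correlations of 0.3 to 0.7. The firm conclusion is that the sign of the stated target depends on how it is read. No particular reversal is established.

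**What to change.** - Delete the rate-of-change rationale from Statistical analyses.
- Keep the two-level multilevel model, with visit as a categorical factor, arm-by-visit terms, and the pre-operative score handled as baseline (constrained equal between arms, or a covariate).
- Name the 3-month arm contrast as the superiority test for hypothesis 2.
- Name the 6-, 12- and 24-month arm contrasts as the equivalence tests for hypothesis 3.

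The cost is wording and a few degrees of freedom. No new data are needed, and hypothesis 2 needs no more men: 90% power at d = 0.5 takes 85 per arm, or 85 / 0.70 ≈ 122 after 30% loss, against 200 planned.

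For the equivalence contrasts, power depends on the margin, which the article does not give. With 140 per arm, a true difference of zero and two one-sided tests at 0.05 each, power = 2Φ(margin / 0.1195 − 1.645) − 1. This is 61% at a margin of 0.3 SD, 91% at 0.4 SD and 99% at 0.5 SD, so the margin in the full plan should be checked against these figures.

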**Methods/design:**

200 men per treatment arm (400 men in total) are being recruited after diagnosis and before treatment through a major public hospital outpatient clinic and randomised to 1) Robotic Prostatectomy or 2) Open Prostatectomy. All robotic prostatectomies are being performed by one surgeon and all open prostatectomies are being performed by one other surgeon. Outcomes are being measured pre-operatively and at 6 weeks and 3, 6, 12 and 24 months post-surgery. Oncological outcomes are being related to positive surgical margins, biochemical recurrence +/− the need for further treatment. Non-oncological outcome measures include: pain, physical and mental functioning, fatigue, summary (preference-based utility scores) and domain-specific QoL (urinary incontinence, bowel function and erectile function), cancer specific distress, psychological distress, decision-related distress and time to return to usual activities. Cost modelling of each approach, as well as full economic appraisal, is also being undertaken.

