To date, case series suggest varied outcomes when comparing robotic with open RP. Some suggest that patients who undergo robotic surgery have less post-operative narcotic use, shorter hospital stays [6] and better short term urinary and sexual function [3,5]. Other studies have found no clear differences in functional outcomes with regards to potency, continence [9], pain and recovery [10]. Finally, the methodological issues that ensue from selection bias in case series and the use of non-standard reporting methods make much of this data difficult to interpret [4,11].

The present study will address this knowledge gap by completing the first randomised trial with men with localised prostate cancer comparing robotic with open RP and assessing QoL and psychosocial outcomes using reliable and previously validated measures of pain, physical and mental functioning, fatigue, summary (preference-based utility scores) and domain-specific QoL (urinary incontinence, bowel function and erectile function), cancer specific distress, psychological distress, decision-related distress and time to return to usual activities. Outcomes are being measured pre-operatively and at 6 weeks and 3, 6, 9, 12, 18 and 24 months post-surgery. Co-morbidity is being considered as a critical issue in deciding who may ultimately benefit from treatment. An economic evaluation is addressing the question of whether open or robotic RP is better ‘value-for-money’, having regard to their comparative costs and outcomes [12-14]. The economic model is integrating the surgical/clinical indices and QoL data from the trial, with the resource costs of the inputs necessary to implement both intervention arms.

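### The rate-of-change model gives the pre-operative score no conditioning role; in its usual forms this makes the visit-specific contrasts for hypotheses 2–4 less precise than they could be

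*Protocol article*

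**What the plan says.** The Statistical analyses section describes the hypotheses as "comparisons of the rate of change with which men in the treatment versus control groups will achieve optimal physical and psychological QoL" and concludes that "the appropriate analysis is a two level multilevel model (with Level 2 = men and Level 1 = Assessment points"). It adds that the analyses will be adapted for equivalence testing where a hypothesis calls for it, but gives no margin. No covariate is named, and nothing is said about how the pre-operative score enters.

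The same section says: "The study design involves a two group Randomised trial with five assessment points". The abstract says: "Outcomes are being measured pre-operatively and at 6 weeks and 3, 6, 12 and 24 months post-surgery", which is one pre-operative and five post-operative assessments. The Background says: "Outcomes are being measured pre-operatively and at 6 weeks and 3, 6, 9, 12, 18 and 24 months post-surgery", which is one plus seven. The count of five therefore matches only the post-operative visits of the abstract.

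In Study aims and hypotheses, hypothesis 2 expects a robotic advantage at 3 months. Hypothesis 3 expects comparable quality of life at 6–12 and 24 months, and hypothesis 4 expects no difference in distress. Under Study integrity, randomisation is stratified by age group and IPSS, not by any quality-of-life or function score other than IPSS.

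**The concern.** The self-report scales are collected before surgery. In a randomised trial the pre-operative score can be used to narrow the interval for the arm effect, and the text as written does not use it that way.

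There are two usual ways to fit what is described:

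- The pre-operative score is one of the Level 1 points. The arm effect is then the arm-by-time term, with each arm free to have its own baseline mean.
- The five points are the post-operative ones, and the baseline has no stated role.

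For a contrast at a given visit, both are less precise than conditioning on baseline. Hypotheses 3 and 4 are the most exposed, because equivalence is decided by interval width. Surgery disturbs urinary and sexual function, so the baseline correlation may be modest for those scales. Below r = 0.5 a change contrast is noisier than ignoring baseline altogether. Conditioning would also deal with chance baseline imbalance in EPIC, IIEF, SF-36 and AQoL-8D, none of which is a stratification factor.

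**Working it through.** **Inputs from the protocol article.** 200 men per arm; at least 70% retained, so 0.70 × 200 = 140 per arm; d = 0.5; alpha 0.05.

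**Assumptions.** Two-sided testing for superiority (the article does not say). Baseline-to-follow-up correlation r = 0.3, 0.5 or 0.7. Equal SD at all visits. The article gives neither a correlation nor an equivalence margin.

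**1. The stated power.** Without any baseline adjustment, d × √(n/2) = 0.5 × √70 = 4.183, and Φ(4.183 − 1.960) = 0.987 (0.986 by noncentral t). This agrees with the claim that "a total sample size if 400 (i.e. 200 per group) would result in over 90% power".

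**2. Variance of a visit-specific contrast** (SD² units, multiplied by 2/n for the arm difference):

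- post-operative score only: 1
- change, baseline means free: 2(1 − r)
- conditioned on baseline: 1 − r²

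| r | Post only | Change | Conditioned | Change ÷ conditioned | Post only ÷ conditioned |
|---|---|---|---|---|---|
| 0.3 | 1 | 1.40 | 0.91 | 1.54 | 1.10 |
| 0.5 | 1 | 1.00 | 0.75 | 1.33 | 1.33 |
| 0.7 | 1 | 0.60 | 0.51 | 1.18 | 1.96 |

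The last two columns are sample-size ratios. Generalised least squares on baseline plus five visits under compound symmetry returns the same change and conditioned variances. It also shows that baseline kept as a response with equal arm means has exactly the conditioned variance: 0.91, 0.75, 0.51.

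**3. Smallest equivalence margin with 90% power** (two one-sided tests at 5%, true difference 0): margin = (1.645 + 1.645) × √(2V/140) = 0.393 × √V.

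| r | Post only | Change | Conditioned |
|---|---|---|---|
| 0.3 | 0.39 | 0.47 | 0.38 |
| 0.5 | 0.39 | 0.39 | 0.34 |
| 0.7 | 0.39 | 0.30 | 0.28 |

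The 0.30 is 0.393 × √0.60 = 0.305; with t quantiles on 278 degrees of freedom it rounds to 0.31.

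**4. Equivalence power at chosen margins**, r = 0.5, 140 per arm, from 2Φ(margin/SE − 1.645) − 1. At this r, change and post-only coincide.

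| Margin (SD) | Not conditioned | Conditioned |
|---|---|---|
| 0.50 | 98.9% | 99.9% |
| 0.40 | 91.1% | 97.4% |
| 0.30 | 61.3% | 79.0% |
| 0.25 | 34.5% | 55.9% |

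**5. The rate-of-change contrast itself.** Take a linear slope over the abstract's six points (0, 1.5, 3, 6, 12, 24 months) under compound symmetry: Σt = 46.5, (Σt)² = 2162.25, Σt² = 767.25. Apart from a common factor, the information on the slope difference is:

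- baseline means free: 767.25 − 2162.25/6 = 406.9
- common baseline mean: 767.25 − r × 2162.25/(1 + 5r) = 507.8, 458.4, 430.9 at r = 0.3, 0.5, 0.7

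The free version therefore has 25%, 13% and 6% more variance. For a slope over the post-operative points alone, the weights sum to zero. If baseline correlates equally with every visit, its covariance with the slope is r × 0 = 0, and conditioning gains nothing.

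**The case against.** The strongest reply is that the article does not say what happens to the baseline. A reader might infer that the plan has chosen to omit the pre-operative score, or to use it as a response instead of conditioning on it. The text supports neither: it lists no covariates, and a multilevel model can carry the pre-operative score at Level 2. Five assessment points even fits five post-operative responses with a pre-operative covariate. Covariate lists are commonly left to the full protocol or analysis plan, which are not shown. This stands, and so the point is not that the article states an error. What remains is that the article does fix a contrast and a model, calls that model the appropriate one, and gives the baseline no conditioning role in it.

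Three other stronger readings also fail:

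- Treating baseline as one more assessment point is not itself a loss. With arm means constrained equal it matches conditioning exactly (step 2).
- The gain does not apply to any contrast. A slope over post-operative points alone gains nothing under compound symmetry, and the slope including baseline gains less than a visit-specific contrast (step 5).
- Not every outcome has a pre-operative score. Time to return to usual activities, in hypothesis 2, has none.

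It is also fair to say that stratifying on IPSS gives some protection on urinary symptoms, and that a covariate needs a rule for men with a missing pre-operative questionnaire.

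**Conclusion.** The point holds as a recommendation to state a more precise method, not as a wrong figure or a contradiction. Followed in its usual forms, the described model gives wider intervals for the visit-specific contrasts that hypotheses 2–4 need. The cost is equivalent to 18–54% more men (change) or 10–96% more (post-operative only) over r = 0.3 to 0.7. Those sizes rest on assumed correlations and on contrasts at named visits.

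A reader might infer that the trial is underpowered. The article does not support that: superiority power at d = 0.5 with 140 per arm is 98.7% post-only and 94.2% in the least favourable change case (r = 0.3). At an equivalence margin of 0.5 SD, every case in step 3 reaches 90% power, since the largest margin required is 0.47 SD. The gain matters mainly if the margins for hypotheses 3 and 4 are tighter than about 0.4 SD, and the article sets none.

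**What to change.** For each self-report scale measured pre-operatively (so not time to return to usual activities), state one of two models:

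- the two-level model fitted to the post-operative assessments, with the pre-operative score of the same scale as a covariate and baseline-by-visit terms; or
- the pre-operative score kept as a Level 1 response, with its mean constrained equal in the two arms.

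The second also keeps men whose pre-operative score is missing; the first needs a stated rule for them. Take the arm contrasts at 3, 6–12 and 24 months from the chosen model. State whether the five assessment points include the pre-operative one, and reconcile that count with the schedules in the abstract and the Background.

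The cost is a sentence or two of analysis wording. The scores are already being collected, and neither the sample size nor the visit schedule need change for the model.

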## Discussion

This research program is addressing key questions of importance by evaluating robotic and open prostatectomy in terms of oncologic parameters, quality of life effects including level of satisfaction, economic costs and overall patient life expectancy; and more broadly by establishing a gold standard for the evaluation of new medical technologies in the clinical treatment of prostate cancer in Australia and internationally. Outputs include evidence to facilitate more effective decision making about surgical treatment for localised prostate cancer and information to support health service planning and development for this rapidly growing patient group.
